### Objectives {7}

Our *primary objective* is to determine whether children diagnosed with a high-risk STEC infection who receive early intravenous fluid administration targeting intravascular volume expansion (i.e., hyperhydration) experience better kidney outcomes as defined by major adverse kidney events within 30 days (MAKE30) compared to children treated with a conservative fluid management approach.

Our *secondary objectives* are to determine whether there are differences in (1) the frequency of life-threatening, extrarenal complications of HUS and (2) the proportion that develops HUS of any severity between participants allocated to receive hyperhydration, compared to those allocated to receive conservative fluid management.

Our *exploratory/tertiary objectives* are to further our understanding of the pathophysiology of HUS and identify predictors of HUS.

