**Fig. 3 Fig3:**
[figure not shown]
The hyperhydration care pathway recommends the infusion of 200% maintenance fluids until a hematocrit reduction of 20% and weight gain of 10% occur. Patients may be discharged if the following criteria are met even if the targets are not achieved: (1) platelet count is > 50 × 10^9^/L (in absence of transfusion) AND they have increased by ≥ 5%* since the preceding test AND (2) absence of diarrhea (loose or watery stool) × 24 h AND (3) ≥ 5 days since the onset of diarrhea. *If > 10 days since the onset of diarrhea, up to a 5% decrease in platelet count since preceding test is acceptable

Reversal of dehydration: initial rehydration strategies should focus on rapidly reversing dehydration.Infusion of 200% of maintenance fluids × 24 h provided, ideally, as a balanced crystalloid (e.g., PlasmaLyte™, Ringer’s Lactate) intravenous solution. Electrolytes and dextrose may be administered as deemed appropriate; customized solutions are permitted. Intravenous fluid solutions containing < 130 mEq/L sodium should be avoided as they increase the likelihood of developing hyponatremia and are less effective in achieving intravascular volume expansion.If the hematocrit reduction is < 20% from the initial value at 24 h, and the weight gain is < 10%, repeat step #2 (infusion of 200% maintenance intravenous fluids for 24 additional hours) unless the weight gain is ≥ 10% in which case move to step #5.Oral fluids permitted ad lib.If the target hematocrit reduction (20% decrease from baseline) AND a 10% weight gain are achieved, adjust total intravenous fluid volume to maintain targeted weight gain and prevent worsening fluid accumulation (i.e., replace insensible losses plus urine and stool output). If both targets are not achieved, then return to step #2.◦ Insensible losses will be estimated to be 400 mL/m^2^ and these losses should be replaced, along with additional losses through output, every 4 to 6 h [39].◦ Daily weights should be performed and be used to guide the assessment of fluid status with additional fluid adjustments made, as required, to maintain the targeted weight gain.Complete blood count, electrolytes, and kidney function should be repeated every 24 h (or more frequently as deemed clinically indicated).Consider nephrology consultation for all children.

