#### Safety targets

Based on the use of this fluid protocol in children with HUS who experienced a mean weight gain of 12.5% without any serious adverse events (SAEs) [18], we have identified parameters ((1) weight gain of 10% AND (2) evidence of hemodilution (i.e., 20% reduction in hematocrit)) which will serve to indicate that intravascular volume expansion has been achieved. This dual parameter approach ensures that hemodilution does not simply reflect hemolysis due to the ongoing microangiopathic process while also identifying a maximal weight gain target to help limit the risk of volume overload.

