#### The hospitalization protocol includes

Reversal of dehydration: initial rehydration strategies should focus on rapidly reversing dehydration.Targeting euvolemia: intravenous fluids should be administered at a maximum rate of 100% maintenance with the rate adjusted to take into consideration ongoing losses (e.g., vomiting, diarrhea, third spacing) and oral fluid intake.◦ The intravenous fluid administered should be isotonic with the volume calculated employing the Holliday–Segar formula [38] with adjustments made as needed to target euvolemia.◦ The fluids provided should be balanced crystalloid (e.g., PlasmaLyte™, Ringer’s lactate) with electrolytes and dextrose added as deemed appropriate; customized solutions are permitted. Intravenous fluid solutions containing < 130 mEq/L sodium should be avoided as they increase the likelihood of developing hyponatremia.Monitoring◦ Daily weights should be performed and be used to guide the assessment of fluid status with additional fluid adjustments made, as required, to maintain euvolemia and weight gain < 5% above baseline.◦ Complete blood count, electrolytes, and kidney function should be repeated every 24 h.Consider nephrology consultation for all children.

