Secondary	Significant extrarenal complications of HUS (life-threatening)	30 days	a. Neurologic i. Seizures requiring anticonvulsant therapy ii. Coma: depressed mental state requiring mechanical ventilation for airway protection and/or ventilatory support iii. Thrombotic or hemorrhagic stroke confirmed by neuroimaging b. Cardiac i. Myocardial infarction: elevated troponin and electrocardiographic features of myocardial ischemia with cardiologist assignment of myocardial infarction ii. Myocarditis: elevated troponin along with cardiologist assigned diagnosis of myocarditis iii. Myocardial dysfunction: reduced ejection fraction requiring inotropic agents iv. Cardiopulmonary arrest requiring cardiopulmonary resuscitation and/or extracorporeal membrane oxygenation v. Arrhythmias requiring electrical or chemical cardioversion or pharmacological anti-arrhythmic therapy c. Respiratory i. Respiratory failure requiring invasive mechanical ventilation (i.e., via an endotracheal tube) ii. Pleural effusions requiring thoracostomy or thoracentesis d. Gastrointestinal i. Hyperglycemia requiring insulin therapy at time of hospital discharge ii. Bowel obstruction/perforation requiring surgical repair iii. Intussusception requiring reduction iv. Acute cholecystitis requiring decompression v. Pancreatitis with lipase > 3.0 × upper limit of normal (ULN) for age vi. Hepatitis/liver failure when any one of the following biochemical criteria are met: bilirubin (when other liver functions are in the normal range) > 3.0 × ULN; bilirubin (when accompanied by any increase in other liver function test) > 1.75 × ULN; AST, ALT, and GGT > 8 × ULN vii. Ascites requiring paracentesis a. Infectious complications i. Bacteremia with or without hypotension requiring inotropic support ii. Peritonitis with or without hypotension requiring inotropic support
Secondary	Development of HUS of any severity (i.e., including those who do not meet the MAKE30 endpoint among those without HUS at randomization)	30 days	HUS is defined as [19]: 1) Anemia (hematocrit level < 30%) AND 2) Thrombocytopenia (platelet count < 150 × 10^3^/mm^3^) AND 3) AKI (serum creatinine concentration > upper limit of reference range for age)

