### Participant timeline {13} (Table 2)

**Table 2 Tab2:**
[figure not shown]
Schedule of activities

^1^Stool testing performed to confirm presence of STEC. If a patient was discharged and found to have a positive STEC result, they may be called back if allocated to a hyperhydration site. Patients meeting criteria will be approached for consent

^2^Collection of data pertaining to treatment administered prior to eligibility being established and consent being obtained, if applicable

^3^Phone, text, or e-mail

^4^Can occur as late as day 37

^5^Zip code

^6^Blood type, screen, & culture (if febrile)

^7^Electrolytes, creatinine, urea nitrogen, lactate dehydrogenase; Incl. method, if performed at an alternate laboratory from the enrollment center

^8^Creatinine labs will be required for those with elevated creatinine at hospital discharge who do not receive RRT or, if out-patient, at the time of study intervention phase discontinuation

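### Incident HUS is judged on a hematocrit cut-off that the hyperhydration pathway deliberately moves, so children with partial HUS can be classified differently by arm without any difference in disease

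*Protocol article*

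**What the plan says.** The second of the two secondary objectives (Objectives {7}) compares "the proportion that develops HUS of any severity between participants allocated to receive hyperhydration, compared to those allocated to receive conservative fluid management".

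Table 1 (Secondary outcomes) defines HUS by three criteria joined by AND: "Anemia (hematocrit level < 30"%), "Thrombocytopenia (platelet count < 150" × 10^3/mm^3) and "AKI (serum creatinine concentration > upper limit of reference range for age"). All three are concentrations or cell counts in a blood sample. The definition is taken from a cited cohort study and asks for no evidence of hemolysis.

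The two pathways treat the first of these measurements very differently:

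- Hyperhydration (Fig. 3 legend): "infusion of 200% maintenance fluids until a hematocrit reduction of 20% and weight gain of 10% occur". The Safety targets section describes the marker of success as weight gain plus "evidence of hemodilution (i.e., 20% reduction in hematocrit").
- Conservative (hospitalization protocol): "intravenous fluids should be administered at a maximum rate of 100% maintenance", aiming for euvolemia and weight gain under 5%, with no hematocrit target.

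Blood counts and kidney function are repeated every 24 hours in both pathways. The HUS analysis is restricted to children without HUS at baseline and uses the same logistic GEE model as the primary outcome, which adjusts for baseline hematocrit and creatinine (Statistical methods {20a}).

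**The concern.** One component of the outcome is a treatment target in one arm. The Safety targets section recognizes that a falling hematocrit may mean dilution or hemolysis, and pairs it with weight gain so that the fluid target is not confused by hemolysis. The outcome definition has no matching safeguard against the opposite confusion, where dilution is read as anemia of HUS.

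The shift arises after baseline and depends on the arm. Excluding children with HUS at baseline and adjusting for baseline hematocrit cannot remove it. A between-arm difference in HUS could then partly reflect plasma volume at sampling. That matters for the inference on one of only two secondary objectives, which the protocol powers at a Bonferroni-corrected alpha of 0.025.

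**Working it through.** **1. The plan's own figure.** Table 4 gives a detectable HUS difference of 6.3 points at 80% power with 26 sites (n = 1040), control rate 17.5%, alpha 0.025. The protocol used simulation for the primary outcome's power table; here a normal approximation is used. Assumptions: two-sided test, 520 per arm, and a cluster-crossover variance factor of 1 − ICC (equal within- and between-period correlation), with ICC 0.106 from Table 3.

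- Effective n per arm = 520/(1 − 0.106) = 582.
- p1 = 0.175, p2 = 0.175 − 0.063 = 0.112, mean 0.1435.
- SE under the null = √(2 × 0.1435 × 0.8565/582) = 0.0206; critical difference = 2.241 × 0.0206 = 0.0461.
- SE under the alternative = √((0.175 × 0.825 + 0.112 × 0.888)/582) = 0.0205.
- Power = Φ((0.063 − 0.0461)/0.0205) = 79.6%, against a stated 80%. The same method gives 89.6% for the 7.1-point difference, against a stated 90%.

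Table 4 is not in error for HUS. It simply takes the outcome to be measured alike in both arms.

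**2. What the 20% target does to the hematocrit criterion.** Diluted value = 0.8 × undiluted value, so the cut-off of 30% corresponds to 30/0.8 = 37.5%.

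| Undiluted hematocrit | At target | Below 30%? |
|---|---|---|
| 35% | 28.0% | yes |
| 37% | 29.6% | yes |
| 40% | 32.0% | no |

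**3. The other two criteria (assumptions needed).** If platelets were diluted by the same factor, counts up to 150/0.8 = 187.5 would read below 150, again toward HUS. If a 10% weight gain spread through body water of 60% of weight, creatinine would be divided by 1 + 0.10/0.60 = 1.17. A true value up to about 1.17 times the age limit would then read as normal, away from HUS.

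**4. Who can change class.** All three criteria are required. Dilution of hematocrit creates a case only in a child who also has low platelets and raised creatinine and whose hematocrit would otherwise have stayed at 30% or above throughout the 30 days. Such children can be enrolled: the exclusion criteria remove only those meeting all three advanced-HUS criteria, so a child with one or two stays eligible. Their frequency is not given.

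**5. Illustration of scale.** Let m be the net excess of hyperhydration children classified as HUS through dilution alone. The documents give no value for m, and 0 is possible. One point is about 5 children (0.01 × 520), against about 91 expected HUS cases in the conservative arm (0.175 × 520). Using the formulas in step 1:

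| m (points) | Power, true reduction 6.3 points | False finding of more HUS, no true effect |
|---|---|---|
| 0 | 79.6% | 1.25% |
| 1 | 61.8% | 3.6% |
| 2 | 41.8% | 8.6% |
| 3 | 24.2% | 17.4% |

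If the creatinine effect dominated and m were −1, −2 or −3, the chance of a false finding of less HUS with no true effect would be 3.7%, 9.3% or 19.9%.

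**The case against.** The strongest reply is that anemia alone does not make HUS. A reader might note that, if baseline hematocrit had mean 37 to 40% and SD 4 (assumed), some 51% to 26% of children would lie between 30% and 37.5%, and infer that this share would be misclassified. The documents do not support that: the share concerns one criterion of three, and a child with diluted hematocrit and normal creatinine is not a case. A child whose disease progresses below 30% anyway is classified the same either way. This part of the reply stands in full.

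Further points also stand. Not every child reaches the 20% target: the hyperhydration steps can move on when weight gain reaches 10%, and Fig. 3 permits discharge without the targets. Both arms reverse dehydration, which itself lowers hematocrit, so the arms differ in degree; it would be too strong to say that dilution occurs in one arm only. The outcome is secondary, and MAKE30 uses neither hematocrit nor platelets.

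It can also be said that sensitivity analyses belong in the SAP, which is not shown. That does not dispose of the point, because the issue is what the stated definition does when applied as written. The as-treated analysis mentioned in the Discussion relates outcomes to fluid received but leaves the HUS definition unchanged.

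**Conclusion.** The point holds in a limited form. As written, the HUS definition can classify a child with partial HUS differently according to arm, because hyperhydration is titrated to a hematocrit fall and the outcome does not separate dilution from hemolysis. The exact part of the size is the band: undiluted hematocrit from 30% to below 37.5%, at full target, in children who also meet the platelet and creatinine criteria.

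Two stronger readings are tempting and should not be drawn. A reader might infer a bias of several points, comparable with the 6.3-point detectable difference; no figure in the documents supports any particular value, and the table in the working is an illustration only. A reader might also infer that the outcome cannot answer its objective, or that it is biased toward harm; since creatinine dilution works the other way, the net direction is unknown. What follows is that a between-arm HUS difference cannot be read cleanly without a supporting analysis. This is worth correcting before the data are analyzed, but it does not touch the primary outcome.

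**What to change.** Keep the cited definition as the main analysis of this secondary outcome. Prespecify a sensitivity analysis of HUS that is less dependent on dilution and identical in both arms. Options are:

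- **(a)** Low platelets plus raised creatinine, without the hematocrit criterion. This removes the component that is titrated, though platelets and creatinine remain open to dilution.
- **(b)** Hematocrit, platelets and creatinine corrected for percent weight gain, with the distribution-volume assumption stated. The outpatient protocol lists no daily weights, so a rule is needed there, such as assuming no gain.
- **(c)** Evidence of hemolysis (LDH, or a smear where one was done) in addition to the current criteria. Table 2 footnote 7 lists "Electrolytes, creatinine, urea nitrogen, lactate dehydrogenase", but LDH is not among the 24-hourly tests in either pathway, and it is itself a concentration that dilution lowers. It should be used where available and described in those terms.

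In each variant, define freedom from HUS at baseline by the same variant. Restricting to values after the expansion phase would not solve the problem, because the pathway then maintains the weight gain.

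State in advance that a between-arm difference in HUS will be interpreted as prevention or harm only if these analyses agree with the main one. The cost is a few lines in the outcome table and SAP and some extra analyses, largely on data already collected, with variants that depart from the cited definition. Care is unchanged.

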### Participant timeline {13} (Table 2)

**Table 2 Tab2:**
[figure not shown]
Schedule of activities

^1^Stool testing performed to confirm presence of STEC. If a patient was discharged and found to have a positive STEC result, they may be called back if allocated to a hyperhydration site. Patients meeting criteria will be approached for consent

^2^Collection of data pertaining to treatment administered prior to eligibility being established and consent being obtained, if applicable

^3^Phone, text, or e-mail

^4^Can occur as late as day 37

^5^Zip code

^6^Blood type, screen, & culture (if febrile)

^7^Electrolytes, creatinine, urea nitrogen, lactate dehydrogenase; Incl. method, if performed at an alternate laboratory from the enrollment center

^8^Creatinine labs will be required for those with elevated creatinine at hospital discharge who do not receive RRT or, if out-patient, at the time of study intervention phase discontinuation

### Sample size

#### Target study sample size

We estimate the overall study sample size required is 1040. The number to be screened will likely be 25% higher given that some children will be ineligible, and some will decline consent. Preliminary data indicate that the primary outcome event rate in the conservative fluid management arm will be approximately 10%. The study will be powered to detect a 5% absolute reduction (risk ratio 0.5) in the rate of MAKE30 in the hyperhydration arm. Using a conservative estimate of 5–15 subjects per year per site, we used simulated data (R software) to generate a power table (Table 3) for a 20- or 26-site cluster-crossover design under varying underlying intra-class correlation (ICC) values. The table shows that power is not highly dependent upon ICC and that 20 and 26 sites are required for 80% and 90% power, respectively, at the ICC estimated from preliminary data (i.e., 0.106) [16]. We expect very low levels of missing data, as participants with elevated creatinine values at the time of discharge will have laboratory follow-up as part of their standard clinical care. Patients who deteriorate and develop the MAKE30 outcome will be readily identified. Thus, the impact of loss to follow-up on power is expected to be minimal.

**Table 3 Tab3:** Power calculations for the primary outcome

Intraclass correlation coefficient	20 cites (approx. 800 subjects)	26 sites (approx. 1040 subjects)
0.05	82%	89%
0.106^a^	81%	90%
0.15	85%	94%

^a^Estimate from preliminary data [16]

The anticipated HUS rate in the conservative fluid management arm is 17.5%, and the rate of extrarenal complications is 7.5%. Detectable absolute differences for these two outcomes with 80% and 90% power, at approximately the same ICC as estimated for the primary outcome, are provided (Table 4). Here, a conservative Bonferroni correction (alpha = 0.025) is used.

**Table 4 Tab4:** Power calculations for secondary outcomes

Outcome	Power	Detectable difference with 20 sites (*n* = 800)	Detectable difference with 26 sites (*n* = 1040)
Hemolytic uremic syndrome—17.5% in conservative fluid management arm	80%	7.2%	6.3%
	90%	8.1%	7.1%
Extrarenal complications—7.5% in conservative fluid management arm	80%	4.7%	4.1%
	90%	5.2%	4.6%

### Recruitment {15}

#### Source of participants

Research teams will seek to be notified and obtain consent to approach all eligible high-risk, STEC-infected children within their catchment area. Study sites are all leading academic tertiary care centers and leads will disseminate their allocated pathway and a desire to serve as a clinical care site for all STEC-infected children. They will connect with satellite institutions and laboratories to be informed of all potentially eligible children. At their local institutions, through mechanisms put in place with their laboratory and all relevant clinical care teams (e.g., ED, infectious disease, nephrology, gastroenterology, pediatrics), the research team will be notified of potentially eligible children. Study teams will take advantage of their electronic medical records to set up reports that inform them of all positive stool tests and relevant diagnoses (i.e., bloody diarrhea, STEC, HUS). The cluster design promotes the initiation of the allocated treatment at any time and does not require research team involvement of participant research consent. The latter can be obtained following treatment implementation. In addition, consent can be obtained for data collection electronically, and as such, children meeting all eligibility can be enrolled without having to come to the study institution (i.e., they can be treated in accordance with the allocated pathway either at a satellite institution or by a care provider who is willing and able to adhere to the pathway).

#### Recruitment venues

Recruitment into the randomly allocated intervention (i.e., hyperhydration vs. conservative fluid management) will occur in the following venues:Emergency departmentsInpatient units: general pediatrics, nephrology, gastroenterology, infectious diseasesMedical microbiology laboratories: partnering laboratories will develop a process to provide the research team with the contact information for the ordering physician so that the allocated pathway can be shared to guide care and to request permission to contact the patient/caregivers of children with positive STEC specimens to obtain research consent. This approach will enable participating sites to recruit participants from their broader geographic catchment area.

#### How potential participants will be identified and approached

Participant identification/approach will vary between sites, but will be based on the following key concepts:Clinician identification: once a child is identified as having a high-risk STEC infection, clinicians will provide patients/caregivers with an STEC information sheet which clearly states that the site is participating in this study, the institution’s treatment approach within the study, and the pros/cons of the two treatment protocols. Clinicians at all sites will be trained to contact the appropriate research team member to determine research eligibility and to obtain permission for the research team to approach the caregiver to request informed consent for data extraction and biospecimen collection.Research team identification:A)Daily screening: reports from the ED and inpatient units will be created to identify all children with potentially eligible chief complaints (e.g., bloody diarrhea, abnormal laboratory result) and discharge diagnoses (e.g., STEC, HUS). Patients infected with a high-risk STEC (evidence of an *E. coli* O157:H7, detection of Stx 2 or a gene encoding this toxin, bloody diarrhea, and presence of Stx or a Shiga toxin gene not otherwise specified, or evidence of early HUS) will be identified (Fig. 5). The research team will approach the clinical team caring for such patients to review research eligibility and to obtain permission to approach the patient for research consent.Medical microbiology laboratory identification: reports identifying all STEC positive stool specimens will be set up. For all children identified potentially eligible children, contact will be initiated by the research team with the responsible physician who will be informed of the sites allocated pathway and who will be asked to obtain consent for the research team to approach the family.

